# 4 STUDY DESIGN

This will be a randomised controlled trial. We aim to recruit a minimum of seventy premature ventilated infants born at less than 31 weeks gestation. Participants will be randomised to either closed-loop automated oxygen control or manually controlled oxygen from recruitment to successful extubation. We will also record basic epidemiologic parameters such as gestation at birth, birth weight, corrected gestational age, day of life and weight at study enrolment, use of antenatal steroids, mode of delivery, doses of surfactant administered, birth plurality and associated comorbidities that may impact on the duration of mechanical ventilation such as open ductus arteriosus and current evidence of infection.

Infants with known congenital anomalies will be excluded from the study.

Informed written consent will be requested from the parents or legal guardians of the infants and the attending Neonatal Consultant will be requested to assent to the study.

**METHODOLOGY**

When the clinical team identifies an infant is eligible for enrolment to the study and following verbal assent of the attending neonatal consultant, a member of clinical staff will initially approach the parents/ legal guardians of eligible infants and if they agree, a researcher. The parents will be provided with an information sheet about the study. The researchers will answer questions and respond to any concerns in a face-to-face meeting. Written informed consent will be obtained.

Eligible infants whose parents consent to the study will be enrolled within 48 hours of initiation of mechanical ventilation. Infants who have not been eligible for recruitment within 48 hours of initiation of mechanical ventilation (for example outborn infants transferred to our unit at a later date) but who remain ventilated on day seven of life and beyond, they will be enrolled to the study immediately after obtaining parental consent.

Randomisation will be performed using an online randomisation generator.

Patients will be ventilated using SLE6000 ventilators. Ventilation settings will be manually adjusted by the clinical team as per unit’s protocol. The intervention group, in addition to standard care will be also connected to the OxyGenie closed-loop oxygen saturation monitoring software (SLE). This software uses oxygen saturations from the SpO_2_ probe attached to the neonate, fed into an algorithm, to automatically adjust the percentage of inspired oxygen to maintain oxygen saturations within the target range. Manual adjustments including the percentage of FiO_2_ will be allowed at any point during the study if deemed appropriate by the clinical team.

The nurse-to-patient ratio will be according to the unit’s protocol that is determined on the patient’s acuity.

Patients will be studied from enrolment until successful extubation [10]. If an infant fails extubation and requires reintubation within 48 hours, he will be studied in his initial arm if less than 28 days old. Therefore, for those infants randomised at the intervention group CLAC will resume. Preterm infants that remain ventilated beyond day 28 of life will continue at their study arm (closed-loop automated oxygen control or manual oxygen control) till their first extubation attempt.

The infant’s clinical team will be present throughout the study to advise and trouble-shoot.

Continuous data will be compared between infants in the intervention group (closed-loop automated oxygen control) and infants in the control group (manual oxygen control). Student's t test will be used for normally distributed data and Mann-Whitney U test for skewed data. Categorical data will be assessed using the Fisher two tailed exact test. P values less that 0.05 will be considered statistically significant. Statistical analyses will be performed using SPSS software (SPSS Inc, Chicago, Illinois, USA).

Notes will be stored in a locked filling cabinet. All identifiable information will be stored in password protected computers and on encrypted devices.

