# STUDY FLOW CHART

Ventilated infants< 31 weeks gestation admitted to NICU at King’s College Hospital

Resume ventilation with Oxygenie if < 28 days old

Randomisation with online computer generated random number

Ventilation with Oxygenie, adjusted by clinical staff as necessary

Screened as eligible by clinical team (no congenital abnormalities)

Parent/ legal guardian approached and consents to the study

Duration of mechanical ventilation

Oxygen saturation and FiO_2_ data from ventilator

Overall time spent on oxygen

Development of BPD

Length of stay

Successful extubation

Reintubation within 48 hours

Extubation to CPAP or NIPPV as per unit’s protocol

Standard ventilation adjusted manually as per unit’s protocol

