**6.1.1 Inclusion criteria**

- Preterm infants less than 31 weeks completed gestation at birth requiring mechanical ventilation and admitted to King’s NICU in the first 48 hours after birth
- Preterm infants less than 31 weeks completed gestation at birth requiring mechanical ventilation on day seven of life and beyond and who have not been eligible for recruitment to the study in the first 48 hours after birth

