**6.2 Sampling**

**6.2.1 Size of sample**

In a cohort of 368 preterm infants born between 24 to 30 weeks gestation, the standard deviation for the duration of mechanical ventilation was 3.83 days [11]. To detect a decrease in the duration of mechanical ventilation of three days with a power of 90% and a significance level of 5%, a sample size of 35 infants in each group would be required.

Historical data from our unit for the period 2015-2020 demonstrated that the median duration of mechanical ventilation for preterm infants born less than 31 weeks gestation was 12 days. Based on the unit’s clinical activity in the most recent years, more than 100 preterm infants less than 31 weeks completed gestation were admitted on average at King’s College Hospital over a twelve month period. An interim analysis will be carried out at half sample size to review if enough data have been gained at that point. The analysis will be performed by an independent researcher not involved in the project to avoid introducing bias to our data. The research team will be blinded to the results of the interim analysis unless there are any significant findings.

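### Early and late (day seven or beyond) entrants share one randomisation and one unadjusted test; entry route is not named as a factor, duration has no time origin, and the sample size makes no visible allowance for the mix

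*Protocol*

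**What the plan says.** **Entry routes.** Under Methodology (section 4), the early route is: "Eligible infants whose parents consent to the study will be enrolled within 48 hours of initiation of mechanical ventilation". The late route takes infants who were not eligible in that window but "who remain ventilated on day seven of life and beyond, they will be enrolled to the study immediately after obtaining parental consent". Section 6.1.1 describes the late group as infants who "have not been eligible for recruitment to the study in the first 48 hours after birth". Its clock therefore starts at birth, whereas the Methodology clock starts with ventilation.

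**Allocation.** Methodology says only: "Randomisation will be performed using an online randomisation generator". The flow chart says: "Randomisation with online computer generated random number". Neither names strata, blocks or minimisation.

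**Analysis.** Methodology plans a t test, or a Mann-Whitney test for skewed data, between the two arms, with the rule "P values less that 0.05 will be considered statistically significant". No term for entry route is mentioned. Section 4 does list day of life at enrolment and gestation at birth among the data to be recorded.

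**Outcome.** Section 3.1 gives the primary outcome as duration of mechanical ventilation and states no time origin. Section 4 and Methodology describe the study period as running from recruitment or enrolment to successful extubation.

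**Sample size.** Section 6.2.1 takes an SD of 3.83 days from an external cohort of 368 infants born at 24 to 30 weeks and arrives at 35 per arm. It also reports a unit median duration of 12 days.

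**The concern.** The late route selects on the primary outcome: an infant qualifies by still needing the ventilator on day seven or later. A late entrant ventilated since birth has about seven days on the ventilator before allocation. If duration counts from intubation, those days enter the outcome, yet the intervention cannot change them. If it counts from enrolment, they drop out, but the SD of 3.83 days may then describe a different quantity from the one analysed.

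In either case, a difference in mean duration between the routes adds to the spread within each arm, and an unadjusted test carries that spread in its standard error. What is at stake is precision, and so the power to detect a 3-day reduction with 70 infants. Timing matters too. A later analysis plan could add a covariate, but it cannot stratify allocations already made.

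The two 48-hour clocks are a related difficulty, because route has to be unambiguous before it can be used as a stratum or a covariate.

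**Working it through.** **Inputs from the protocol (6.2.1 and Methodology).** Difference 3 days, SD 3.83 days (variance 3.83² = 14.67), 90% power, 5% significance, 35 per arm.

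**Inputs not in the protocol.** The late share *p* and the gap *D* in mean duration between routes. Both are assumed below and shown over a range.

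**Step 1: the planned figure.** With a two-sided 5% level, n per arm = 2 × (1.960 + 1.282)² × 14.67 / 3² = 34.3, so 35. The stated size reproduces (a one-sided level would give 28). Power of the t test at 35 per arm is 89.8%.

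**Step 2: effect of the mix.** If 3.83 is the SD within each route, pooling adds variance *p*(1 − *p*)*D*², and the SD in the unadjusted test becomes √(14.67 + *p*(1 − *p*)*D*²). For *p* = 20% and *D* = 5, the added variance is 0.20 × 0.80 × 25 = 4.0 and the SD is √18.67 = 4.32. Other cases, with t-test power at 35 per arm:

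| Late share | Gap (days) | Added variance | SD | Power |
| --- | --- | --- | --- | --- |
| 10% | 5 | 2.25 | 4.11 | 85% |
| 10% | 7 | 4.41 | 4.37 | 81% |
| 20% | 3 | 1.44 | 4.01 | 87% |
| 20% | 5 | 4.00 | 4.32 | 82% |
| 20% | 7 | 7.84 | 4.74 | 74% |
| 20% | 10 | 16.00 | 5.54 | 61% |

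**Step 3: when would the added variance exceed the planned variance?** This requires *D* > 3.83 / √(*p*(1 − *p*)): 12.8 days at 10% late, 9.6 at 20%, 8.4 at 30% and 7.7 at 50%. At a 7-day gap the added variance is at most 0.25 × 49 = 12.25, below 14.67 whatever the late share.

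**Step 4: how small could the loss be?** Suppose durations are normal with centre 12 (the unit median) and SD 3.83. Infants ventilated beyond day 7 then have a mean only 0.72 day above the overall mean. At 20% late the added variance is 0.16 × 0.72² = 0.08, and power stays at about 90%.

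**Step 5: chance imbalance.** With 14 late entrants (20% of 70) and simple randomisation, a split of 9–5 or worse has probability 2 × P(X ≤ 5) = 2 × 3473/16384 = 0.42, with X binomial(14, ½). At a 10-day gap a 9–5 split moves the arm difference by (9 − 5)/35 × 10 = 1.14 days. This variation is already part of the standard error used in step 2, so it is not a further loss.

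**Step 6: the clocks side by side.** Take an infant admitted after 48 hours of life and first intubated on days 3 to 6. Methodology allows early enrolment, because its 48 hours start with ventilation. Section 6.1.1 does not admit that infant unless ventilation is still needed on day seven. For an inborn infant the conflict depends on whether the 48 hours in the first inclusion bullet qualify only admission.

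**The case against.** The strongest reply is that the size of the problem rests on two numbers the documents do not give. That stands. A reader might infer that the mix must add more variance than the whole planned figure. Step 3 shows that this needs a large gap, and at 7 days it fails for every late share. With a unit median of 12 days, many early entrants will also be ventilated past day seven, so the gap may be small (step 4). A skewed distribution would widen it: an exponential with median 12 gives a 7-day gap. But its SD is about 17 days, and the planned SD itself would then be the problem rather than the mix.

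The 3.83 days is quoted for a whole cohort, which may already include infants ventilated beyond a week. Adding the mix on top could count it twice. This also stands, and it is why every power figure is conditional.

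A reader might also take it as settled that pre-randomisation days are counted. The protocol does not say so, and its description of the study period leans towards counting from enrolment. On that reading the gap could shrink or reverse. The fair criticism is that the origin is undefined.

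Nor does the protocol state that allocation is simple and unblocked; it is silent on the scheme. Adjustment may sit in an analysis plan not shown here. That reply does not reach the allocation, which has to be fixed before the first infant is randomised.

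Finally, chance imbalance might be read as a source of false positives. It is not: it lies within the standard error and does not inflate the type I error.

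**Conclusion.** The point holds in a conditional form. The protocol admits two routes, one of them selected on continuing ventilation. It names no stratification, states an unadjusted test, sizes the trial on one SD with no visible allowance for the mix, and leaves the time origin of its primary outcome open. If 3.83 days is the within-route SD and 20% of infants enter late, power would be about 82%, 74% or 61% for gaps of 5, 7 or 10 days, against the planned 90%. If the gap is small, or 3.83 already covers the mix, the loss could be negligible. The documents do not settle which case applies, so confidence attaches to the design gap and not to any single power figure. The issue is lost precision, not bias or an inflated error rate. The change is worth making because it costs little and its allocation part cannot be made afterwards. The differing 48-hour clocks are a minor but real ambiguity.

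**What to change.** 1. In section 3.1, define the primary outcome as days of mechanical ventilation from randomisation. In 6.2.1, say which duration and which infants the 3.83-day SD describes.
2. In Methodology, replace the general reference to an online generator with a concealed list in random permuted blocks, stratified by entry route.
3. Include entry route and gestation at birth as covariates in the primary analysis. Stratifying alone would not suffice, because pooling creates the extra variance and an unadjusted t test would still carry it. If the within-route SD is 3.83, adjusting for route brings power back to about 90%.
4. Reconcile the 48-hour clock between Methodology and 6.1.1, so that every infant belongs to one route only.

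The cost is a one-off set-up of the stratified list and one more term for route in the analysis. Gestation and day of life at enrolment are already to be recorded, and no extra infants are needed.

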**3.1** **Objectives**

The primary objective of this study is to compare the duration of mechanical ventilation in preterm infants receiving closed-loop automated oxygen control with those receiving manually-adjusted oxygenation.

Secondary objectives are to evaluate any differences between the two groups in time spent in target oxygen saturation ranges, incidence of hypoxia or hyperoxia, manual adjustments required by clinical staff and adverse outcomes including BPD (at 36 weeks post menstrual age), overall duration of oxygen supplementation and length of stay.

- 1. **Outcome**
- Our primary outcome is the duration of mechanical ventilation
- Secondary outcomes are:

-percentage of time spent in target saturation range

-time spent in hypoxia and hyperoxia

-number of manual adjustments required

-number of days on oxygen

-diagnosis of BPD at 36 weeks post menstrual age

-length of ICU stay

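### The stated comparison is unadjusted and its test is picked from the data, although gestation and age at enrolment are recorded; one adjusted primary analysis would be more efficient at no cost

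*Protocol*

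**What the plan says.** The primary outcome is set in Protocol section 3.1: "Our primary outcome is the duration of mechanical ventilation". The statistical paragraph at the end of Methodology (section 4) covers all continuous data in one sentence: "t test will be used for normally distributed data and Mann-Whitney U test for skewed data". It has no separate rule for the primary outcome and names no covariate.

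Section 4 also lists the baseline data: "We will also record basic epidemiologic parameters such as gestation at birth, birth weight, corrected gestational age, day of life and weight at study enrolment". Further items follow, ending with comorbidities such as open ductus and infection. No section gives any of them a part in the analysis.

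Methodology and section 6.1.1 admit infants by two routes. One is early, within 48 hours. The other is for infants still ventilated on day seven of life or later who could not be recruited early.

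On allocation, Methodology says "Randomisation will be performed using an online randomisation generator", and the study flow chart says "Randomisation with online computer generated random number". Neither mentions blocks, strata or minimisation.

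Section 6.2.1 plans the sample on an unadjusted comparison of means: "the standard deviation for the duration of mechanical ventilation was 3.83 days" in a cited cohort, a target difference of three days, 90% power and a 5% level, from which "a sample size of 35 infants in each group would be required".

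**The concern.** There are two weaknesses.

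First, any part of the variation in ventilation time that is predictable at enrolment stays in the error term of an unadjusted test. It is reasonable to expect gestation to be such a factor in infants from the least mature up to 30 completed weeks, though the protocol does not say so. Entry route is a clearer case. Late entrants qualify because they are still ventilated on day seven or later, so the eligibility rule itself ties entry route to the outcome. Neither the stated allocation nor the stated analysis takes account of it.

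Second, the observed distribution decides which test is primary. The t test compares means, and the Mann-Whitney test compares ranks. Until the data are seen, the quantity that the trial estimates is not settled.

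At stake are precision that the trial could have without recruiting more infants, and the credibility of a small single-centre result if the arms happen to differ in maturity or in the share of late entrants.

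**Working it through.** **Inputs from the protocol (section 6.2.1):** difference 3 days, SD 3.83 days, power 90%, level 5%, 35 per arm. Sidedness is not stated for this test. Two-sided is taken because it reproduces 35 (one-sided gives 28).

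**Assumptions, not in the protocol:** correlation r between the baseline factors together and duration, shown at 0.5 and 0.7; true SD, shown at 6 and 8 days besides the planned 3.83.

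**1. The plan's own figure.** n per arm = 2 × (SD × (1.960 + 1.282) / 3)² = 2 × (3.83 × 3.242 / 3)² = 34.25, rounded up to 35. This agrees with the protocol. Power at 35 per arm is 89.8% by the noncentral t distribution (90.6% by the normal approximation).

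**2. Effect of adjustment on sample size (linear model).** Residual SD = SD × √(1 − r²), so the required n is multiplied by (1 − r²).
- r = 0.5: 34.25 × 0.75 = 25.7, about 26 per arm.
- r = 0.7: 34.25 × 0.51 = 17.5, about 18 per arm.

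**3. Effect on power at 35 per arm (noncentral t, residual SD as above).**

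| SD (days) | Unadjusted | r = 0.5 | r = 0.7 |
| --- | --- | --- | --- |
| 3.83 (planned) | 90% | 96% | 99% |
| 6 (assumed) | 54% | 66% | 82% |
| 8 (assumed) | 34% | 43% | 58% |

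Share of the shortfall from 90% that adjustment recovers:
- SD 6: (66 − 54)/(90 − 54) = 33% at r = 0.5, and (82 − 54)/36 = 78% at r = 0.7.
- SD 8: (43 − 34)/(90 − 34) = 16% at r = 0.5, and (58 − 34)/56 = 43% at r = 0.7.

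Adjustment helps in every row, but at SD 8 it closes less than half of the gap even at the higher correlation.

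**4. Chance imbalance without stratification.** With 35 per arm, the standardised difference in a baseline factor has SD √(2/35) = 0.24. It exceeds 0.3 in either direction with probability 2 × P(Z > 0.3/0.239) = 21%. If 14 of the 70 infants were late entrants (assumed), the arms would split them 10:4 or worse in 13% of allocations (hypergeometric).

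**5. Unequal arm sizes.** If allocation were simple, a 30:40 split or worse would occur with probability 28% (binomial, 70 infants, one half). At 30:40 and SD 3.83, power is 89.2% against 89.8%, a loss of under one percentage point. Unequal arms are therefore not a reason to change the plan.

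**The case against.** The strongest reply is that nothing is broken. The unadjusted test is valid under randomisation, and its 5% error rate already allows for chance imbalance. On the protocol's own inputs the trial has 90% power. A statistical analysis plan, not shown here, may add an adjusted model, and the sentence on tests is generic and does not exclude one. All of this stands, and it limits the point to efficiency and to fixing the primary test. It does not remove the point, because the only comparison that the protocol names is unadjusted and its choice is left to the data.

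A reader might infer four stronger things that the document does not support:
- **That power has been lost and adjustment would recover much of it.** A loss needs an SD above 3.83, and the protocol gives none. Its unit median of 12 days and its rules for infants ventilated beyond day 28 make a larger spread plausible but do not give its size. If the SD is well above plan, adjustment recovers only a minority of the shortfall.
- **That randomisation is simple.** The wording is compatible with that, but an online generator can also produce a blocked list. What can be said is that blocking and stratification are not mentioned.
- **That the protocol itself calls gestation prognostic.** Its remark about influence on ventilation time attaches most directly to comorbidities.
- **That an uneven split would endanger the trial.** It would cost almost nothing, as shown above.

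One further objection is fair. The figures here are for a linear model on days. A proportional-odds model or a model on log duration has a different effect measure, and its power has not been computed.

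**Conclusion.** The point holds as a recommendation to improve efficiency and to fix the primary test. It is not an error or a contradiction. At the planned SD of 3.83, an assumed correlation of 0.5 is worth a fall from 35 to about 26 infants per arm, or a rise in power from 90% to about 96%. The gain depends wholly on a correlation that the documents do not give. It would be near zero if the covariates did not predict duration, and then the cost would be negligible too. The case for including entry route is firmer than the case for any particular correlation, because the eligibility criteria link it to the outcome. Adjustment should not be presented as a remedy for an SD that proves much larger than planned.

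**What to change.** 1. Prespecify one primary analysis of duration of ventilation, adjusted for gestation at birth and for entry route or age at enrolment. Two suitable choices are a proportional-odds model (the covariate-adjusted counterpart of the Mann-Whitney test) or ANCOVA on log duration.
2. State the effect measure that goes with it: an odds ratio for the first, a ratio of durations for the second. Neither is the 3-day difference in section 6.2.1, so that section should say how the planned effect relates to the chosen measure.
3. Keep the unadjusted test as a sensitivity analysis, and name now which one it is rather than leaving the choice to the observed distribution.
4. State the allocation method. If it is stratified, use a concealed permuted-block list with few strata, because 70 infants divided by gestation band and entry route could leave sparse late-entry cells. Include those strata in the model.

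The analysis change costs nothing in infants or data collection: the covariates are already recorded, and SPSS, the software that the protocol names, fits these models. A blocked list takes about an hour to prepare.
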